***2.3 Other pre-specified study endpoints***

As explorative endpoints, we will also consider changes (per month) in: protein and energy intake, Mini Nutritional Assessment (MNA®) score, C-reactive protein, vitamin D, total cholesterol, albumin and creatinine.

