## *6.1 Assessments*

The following assessments will be performed throughout the study as indicated above:

*Medical History & Demographics.* Information will be collected on age, gender, main admission diagnosis, number of comorbidities and medications.

*Nutritional Assessment:* body weight (to the nearest 0.1 kg) and height (to the nearest 0.5 cm) will be measured according to standard procedures and body mass index (BMI) will be derived accordingly (*Anthropometry*). A trained dietitian will be responsible for the evaluation of calorie and protein intake. At study inclusion a 24-h dietary recall (with the aid of the caregiver) will be performed with the help of a food atlas, while at the end of study a calibrated dietetic spring scale will be used to weigh all foods served and returned on consecutive days. A computer program (DR3 v3.1.0; Sintesi Informatica Srl, Milano, Italy) will be used to estimate the energy and the macronutrient content of food consumed (*Protein-calorie intake*), including nutritional supplementation. Finally, nutritional status will be rated by means of the *Mini Nutritional Assessment* (MNA®), a brief questionnaire based on an anthropometric assessment (BMI and weight loss), a general assessment (lifestyle, medication, and mobility), and a dietary assessment (number of meals, food and fluid intake, self-assessment of autonomy of eating, and self-perception of health and nutrition).

*Muscle mass (body composition)*: in the screening phase, the presence of low skeletal muscle mass will be diagnosed [(skeletal muscle mass/body weight  100) ≤37% in men and ≤28% in women] using bioelectric impedance analysis (BIA 101; Akern s.r.l., Florence, Italy). Then, appendicular muscle mass (AMM) and total body skeletal muscle mass (for the calculation of skeletal muscle mass index [SMMI]) will be evaluated using Dual-energy X-ray absorptiometry (DXA; Lunar Prodigy, GE Medical Systems).

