# **Statistics and sample size**

***8.1 Sample size***

In the absence of preliminary data to estimate the expected treatment difference, the sample size was set at 128 patients reaching the evaluation of the primary endpoint (64 per arm) to achieve a statistical power of 80% (type I error 5% using a two-tailed test) to detect a clinically meaningful difference (mean treatment difference/standard deviation [effect size]=0.5). Allowing for a 10% drop-out rate in each arm, it was decided to randomize 140 patients (70 per treatment arm).

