***8.2 Statistical analysis***

The efficacy analysis population will include the patients reaching the primary endpoint evaluation and it will be performed according to the intention to treat principle.

All patients consuming at least one serving of nutritional formula will be included in the safety analysis.

Descriptive statistics: Mean and standard deviation, range, median and quartiles will be calculated for continuous variables. Frequencies and percentages will be calculated for categorical variables.

Analysis of study endpoints: Expecting a treatment effect also on the LOS, changes over time in both primary and secondary continuous outcome variables will be normalized by the duration of observation in months. Changes will be calculated so that an improvement would result in a positive value in favor of the experimental formula (as either final - initial value or initial - final values).

*Primary endpoint* - The change in gait speed will be compared between groups with a generalized linear regression model using Huber-White robust standard errors to account for variance inhomogeneity. Then a series of supportive analyses of the primary endpoint will be performed. First, we will conduct a multivariable model, to adjust for potential confounders regardless of differences in baseline features, including gender, age and monthly change in energy intake, creatinine and in total cholesterol. Second, a conservative sensitivity analysis of the primary endpoint using the worst possible outcome of the study for patients dropping out will be performed.

*Secondary endpoints* - Group comparison will be performed for all secondary endpoints on a continuous scale using an unadjusted generalized linear regression model. For both primary and secondary outcome variables the mean change within groups will be also assessed. For secondary endpoints on a binomial scale, a generalized linear model for the binomial family will be used. For all endpoints the treatment effect (mean or frequency difference) and 95% confidence interval (CI) will be reported.

All statistical analyses will be performed using the software STATA 15.0 statistical software (Stata Corporation, College Station, TX).

Dropout

The following causes of dropout will be considered:

- Death

- Lost to follow-up (due to hospitalization or transfer to another setting of care)

- Withdrawal

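### The first supportive model of the primary endpoint adjusts for three post-randomisation changes as if they were confounders, so it can remove or distort the treatment effect if the formula moves them

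*Protocol*

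**What the plan says.** Section 8.2 makes an unadjusted group comparison with Huber-White standard errors the primary analysis of gait-speed change. The first supportive analysis is a multivariable model. Its stated purpose is to deal with possible confounding whatever the baseline balance, and its covariates are fixed: "including gender, age and monthly change in energy intake, creatinine and in total cholesterol".

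Four other places bear on these covariates:

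- Section 2.3 lists the per-month changes in energy intake and in "vitamin D, total cholesterol, albumin and creatinine" among the exploratory endpoints.
- The assessment table under Methods has dietary intake and biochemistry measured at baseline and at end of study, so a change is known only after treatment.
- Section 6.1 says that software "will be used to estimate the energy and the macronutrient content of food consumed", and it counts the study supplement in that intake.
- Section 5.2 gives the active arm 150 kcal and 20 g of whey protein per serving, twice daily. The control is a maltodextrin powder of equal calories.

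Sections 6.2 and 8.2 divide changes by months of observation and expect treatment to alter the length of stay. Nothing labels the multivariable model as a mediation or direct-effect analysis.

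**The concern.** A confounder of a treatment comparison must influence, or share a cause with, the allocation. Randomisation rules that out for anything that happens later. A change measured at discharge can stand in only three relations to the gait result:

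- It lies on the path from formula to gait speed.
- It is affected by the formula and shares an unmeasured cause with gait speed, such as intercurrent illness.
- It is unaffected by the formula.

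Adjustment removes part of the effect in the first case and biases the estimate in the second. Only in the third is it harmless. By listing the same three changes as endpoints, the protocol itself treats an effect of the formula on them as an open question.

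This is the only covariate-adjusted model specified for the primary endpoint, and readers will use it to judge robustness. If the covariates move with treatment, it no longer estimates the effect of the randomised formula. It may then disagree with a correct primary result or seem to support a wrong one.

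**Working it through.** **1. The plan's own figure.** Section 8.1 gives "type I error 5% using a two-tailed test", a power target of 80% and "mean treatment difference/standard deviation [effect size]=0.5". The normal approximation gives 2 × (1.960 + 0.842)² / 0.5² = 62.8, so 63 per arm. The t-test gives 63.77, so 64 per arm, with 80.1% power. This reproduces "128 patients reaching the evaluation of the primary endpoint (64 per arm"). The figure belongs to the unadjusted comparison, and the present point leaves it unchanged.

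**2. Timing and role of each covariate.**

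| Covariate in 8.2 | When known | Also an endpoint in 2.3? |
|---|---|---|
| Gender | Baseline | No |
| Age | Baseline | No |
| Change in energy intake | End of study | Yes |
| Change in creatinine | End of study | Yes |
| Change in total cholesterol | End of study | Yes |

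**3. What adjustment does to the estimate.** Scale gait change and the covariate to a within-arm SD of 1. Let Δ be the true total effect, *a* the effect of treatment on the covariate, and *s* the within-arm slope of gait change on the covariate. In a linear model:

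adjusted coefficient = Δ − *a* × *s*

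The slope *s* may be causal (the covariate affects gait) or may come from a shared cause, in which case it is the product of the two loadings. The documents give neither *a* nor *s*, so every value below is assumed. The simulated figures use 64 per arm, robust standard errors and 4,000 runs. The last two rows are the exception: they come from one large sample of 200,000.

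| Case | Δ | *a* | *s* | Δ − *a*·*s* | Simulated | Rejections at 5% |
|---|---|---|---|---|---|---|
| Covariate not moved | 0.5 | 0 | 0.4 | 0.50 | 0.50 | 85% |
| On the path | 0.5 | 0.25 | 0.2 | 0.45 | 0.45 | 72% |
| On the path | 0.5 | 0.25 | 0.4 | 0.40 | 0.40 | 67% |
| On the path | 0.5 | 0.5 | 0.2 | 0.40 | 0.40 | 60% |
| On the path | 0.5 | 0.5 | 0.4 | 0.30 | 0.30 | 44% |
| Opposite shift | 0.5 | −0.5 | 0.4 | 0.70 | 0.69 | 98% |
| Shared cause, 0.5 × 0.5 | 0.5 | 0.5 | 0.25 | 0.375 | 0.38 | 56% |
| Shared cause, opposite shift | 0.5 | −0.5 | 0.25 | 0.625 | 0.62 | 94% |
| Shared cause, no true effect | 0 | 0.5 | 0.25 | −0.125 | −0.13 | 11.6% |
| Shared cause, 0.6 × 0.5 | 0 | 0.5 | 0.30 | −0.15 | −0.149 | – |
| Shared cause, 0.6 × 0.5 | 0 | 1.0 | 0.30 | −0.30 | −0.297 | – |

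The unadjusted model gives about 0.50 SD and 80% power in every row with Δ = 0.5. In the null rows a positive shift biases against the formula. Reversing the sign of *a* reverses the sign of the bias.

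**4. The shared divisor.** Outcome and covariates are all expressed per month of the same stay. Assume the same raw gait gain of 0.1 m/s in both arms and mean stays of 1.2 and 1.5 months. The unadjusted difference is then about 0.016 m/s/month. Adjustment changes it to 0.016, 0.015 or 0.012 as the mean raw covariate change is set to 1, 2 or 4 SD, and leaves it alone when that mean is 0. This route exists but is small.

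**The case against.** The strongest reply is that little depends on this model. The primary test is unadjusted, no success rule uses the multivariable result, and the sample size was set for the unadjusted comparison. All of that stands. A reader might infer that the primary result is compromised, and the documents do not support that.

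A second reply concerns energy intake. Because intake counts the supplement, a reader might infer that the covariate separates the arms by construction. It should not: the control is isocaloric, so full intake adds 2 × 150 = 300 kcal/day in either arm. What remains is a possible difference in other food eaten, in compliance or through the duration divisor. The reply does not reach creatinine or cholesterol, because the two powers of equal calories differ in composition, whey protein against maltodextrin.

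A third reply is that bias needs both *a* and *s* to differ from zero, and the documents report neither. This also stands. It rules out saying that the model does remove the effect, but not that it can. A model offered as support should not depend on the formula having no effect on three of the trial's own endpoints.

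The absence of baseline gait speed from the list is not an error. Leaving a prognostic covariate out of a randomised comparison does not bias it.

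**Conclusion.** The point holds as a fault in a supportive analysis. Three of the five covariates are post-randomisation changes, are listed as endpoints and are wrongly described as confounders. No other passage repairs this. If the formula moves them, the model does not estimate the effect of the randomised formula.

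The size and sign of the bias cannot be derived from the protocol. Under the assumed linear relations, a true 0.5 SD becomes 0.45–0.30 SD when the covariate lies on the path (shift 0.25–0.5 SD, slope 0.2–0.4), and about 0.69 SD with an opposite shift. A null effect becomes about −0.15 to −0.30 SD with a shared cause (shift 0.5–1 SD, loadings 0.6 and 0.5), or the same size with a positive sign if the shift is reversed. These are illustrations and not likely ranges. With no shift there is no bias. The correction should be made, but the validity of the primary comparison does not depend on it.

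**What to change.** In section 8.2, limit the supportive model to baseline covariates: gender, age and, since they are already measured, baseline gait speed, energy intake, creatinine and total cholesterol. Delete the three change terms. Randomisation makes the expected shift in a baseline covariate zero, which is the first row of the table: the estimate stays at 0.50 SD, with power of about 80%, or 85% if the covariate is prognostic with slope 0.4.

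If a model with the changes is still wanted, report it separately as exploratory mediation, state its assumptions, and do not present it as support for the primary result.

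The cost is one sentence in 8.2. No new data, visits or patients are needed. The change should be made before the treatment codes are unmasked, so that the covariate choice is not open to dispute later.

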# **Study design**

A single-site, interventional, randomized (1:1), parallel-group, double-blind, controlled, 8-week clinical trial.

Expected study duration: 24 months.

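### The dropout sensitivity analysis in section 8.2 is conservative only if control dropout does not materially exceed experimental dropout

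*Protocol*

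**What the plan says.** Section 8.2 defines the main efficacy comparison on completers: "The efficacy analysis population will include the patients reaching the primary endpoint evaluation". It continues: "Then a series of supportive analyses of the primary endpoint will be performed". Two such analyses are named. The first adjusts for covariates. The second is "a conservative sensitivity analysis of the primary endpoint using the worst possible outcome of the study for patients dropping out will be performed".

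The rule names no arm and refers to the outcome of the study as a whole, so the plain reading is one common value for dropouts in either arm. Changes are scored so that improvement is positive, which makes the worst outcome the lowest monthly change. Dropout covers death, loss to follow-up through hospitalisation or transfer, and withdrawal, with one list for both arms. Section 8.1 plans for equal losses: "Allowing for a 10% drop-out rate in each arm, it was decided to randomize 140 patients (70 per treatment arm"). Nothing in section 8.2 addresses an unequal split.

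**The concern.** An analysis called conservative should not be able to move a null result towards the product. This one can. Each dropout pulls down the mean of the patient's own arm, so an excess of control dropouts pulls the control mean down further and widens the difference in favour of the experimental formula.

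The main comparison leaves dropouts out, and the covariate-adjusted analysis does not restore them. Within the protocol, this run is therefore the only check on missing primary data. If the control arm lost clearly more patients, a positive result could be reported as conservative confirmation although the imputation rule had produced part of it.

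**Working it through.** **Inputs from the protocol.** 1:1 allocation, 140 randomised (70 per arm), 128 evaluable (64 per arm), effect size 0.5 SD, two-sided 5% (2.5% in each direction), 80% power, 10% dropout per arm (7 of 70).

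**Assumptions, not in the protocol.** Normal outcome with SD 1. Worst value *w* equal to the lowest observed value in the trial, which averages about −2.59 SD with no effect and −2.41 SD with a true 0.5 SD. I also tried fixed values of *w* from −2 to −3 SD.

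**The plan's own figure.** A normal approximation for 0.5 SD gives 63 per arm. The t-test with 64 per arm has power 0.801, so 128 reproduces. Ten per cent dropout from 140 leaves 126 rather than 128, which is immaterial.

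**Formula.** Let mE and mC be the completer means and dE and dC the dropout fractions. After imputation the difference is

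(1 − dE)·mE + dE·w − (1 − dC)·mC − dC·w,

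so the shift from the completer difference is

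**dC·(mC − w) − dE·(mE − w).**

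**No true effect** (mE = mC = 0). The shift reduces to (dC − dE)·(−w).
- 5 v 9: (4/70) × 2.59 = +0.15 SD (range +0.11 to +0.17 for *w* from −2 to −3).
- 4 v 10: (6/70) × 2.59 = +0.22 SD (range +0.17 to +0.26).

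**True effect 0.5 SD** (mE = 0.5, mC = 0, w = −2.41).
- 7 v 7: 0.10 × 2.41 − 0.10 × 2.91 = −0.05, so the estimate is 0.45.
- 7 v 8: (8/70) × 2.41 − (7/70) × 2.91 = 0.275 − 0.291 = −0.016, so the estimate is about 0.48.
- The estimate exceeds the completer value only if dC/dE > (mE − w)/(mC − w) = 2.91/2.41 = 1.21 (1.17 to 1.25 for *w* from −3 to −2). The ratio 8/7 = 1.14 falls short; 8/6 = 1.33 passes.

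**Simulation.** 40,000 trials per setting, 70 per arm, unequal-variance standard errors, cut-off 1.96.

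| Dropouts, experimental v control | No effect: estimate (SD) | No effect: significant for experimental (nominal 2.5%) | True 0.5 SD: estimate | True 0.5 SD: power |
|---|---|---|---|---|
| 7 v 7 | 0.00 | 0.6% | 0.45 | 59% |
| 7 v 8 | +0.04 | 0.9% | 0.48 | 66% |
| 6 v 8 | +0.07 | 1.9% | 0.53 | 76% |
| 5 v 9 | +0.15 | 5.7% | 0.60 | 88% |
| 4 v 10 | +0.22 | 13.2% | 0.68 | 95% |
| 3 v 11 | +0.30 | 25.6% | 0.75 | 98% |
| 10 v 4 | −0.22 | 0.01% | 0.22 | 11% |

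Completer power is about 80% throughout. A separate set of 10,000 trials per setting with Welch tests gave 5.0% at 5 v 9 and 12.4% at 4 v 10. Every row except 7 v 8 has 14 dropouts in total, the overall 10% that section 8.1 allows; only the split differs.

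**Dropout left to chance.** With each patient at 10% risk in both arms and no true effect, the mean estimate is −0.001 SD, with 2.55% of trials significant for the experimental formula and 2.53% for control. With a true 0.5 SD the estimate is 0.45 and power 57%. A control excess of 6 or more arises in 6.0% of such trials. If the underlying risks really differ, at 4/70 and 10/70, the false-positive rate is about 18%.

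**The case against.** Four points on the other side have weight.

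- **The rule is conservative as planned.** Section 8.1 assumes equal dropout, and there the rule shrinks the effect and cuts power. If dropout risk is equal and splits by chance, there is no average bias and no excess error. This stands: inflation needs a real difference in dropout risk, or an unlucky split, and the protocol predicts neither.
- **A common worst score can be a legitimate composite.** Death is a bad outcome in itself, and excess control deaths would be signal rather than bias. This stands for deaths. It does not carry over automatically to withdrawals or transfers, which the protocol treats in the same way.
- **The analysis is only supportive.** This stands; the primary test does not change.
- **The SAP may add other scenarios.** It may, so the statement that this is the only check applies to the protocol alone. But the protocol itself fixes the rule and claims the property.

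A reader might also infer more than the documents support:

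- *That the rule favours the product whenever control loses more patients.* With a true 0.5 SD effect, 7 v 8 still lowers the estimate. With no effect, the false-positive rate stays below 2.5% at both 7 v 8 and 6 v 8, because the repeated extreme value inflates the variance.
- *That the worst monthly change will probably come from a short-stay patient with a small denominator.* The programme runs 4 to 8 weeks, so denominators among those completing it differ by about twofold at most. Nothing in the protocol links early completion to the largest losses.

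**Conclusion.** The concern holds in qualified form. The property claimed in section 8.2 is not built into the rule; it depends on how dropouts divide between the arms. With equal dropout, or more experimental dropout, the rule works against the product. With a clear control excess, roughly 9 v 5 or more of 70, it works for the product: about +0.15 SD and 5–6% false positives at 5 v 9, and about +0.22 SD and 12–13% at 4 v 10, with no true effect and a nominal 2.5%.

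The sizes rest on the assumed normal outcome, SD 1 and worst observed value. The direction follows from the formula alone. Reading the worst outcome as a theoretical extreme beyond the observed range would enlarge the shift. The consequence is limited to how robust the primary result is said to be.

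**What to change.** In section 8.2:

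1. Add an arm-asymmetric run: worst observed value for experimental dropouts, control completer mean for control dropouts. Its shift from the completer estimate is −dE·(mE − w), which is never in favour of the product. Section 7.2 keeps the codes masked as A and B during analysis, so run it in both directions.
2. Take the control arm's standard error in that run from its completers. Filling in means makes it too small: with 7 of 70 filled in, about √(0.9/70) = 0.113 instead of √(1/63) = 0.126.
3. Report dropouts by arm and cause beside the result.
4. If the common-value run is kept, describe it as a common worst-value (composite) analysis and drop the word conservative.

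A tipping-point analysis is optional. The protocol plans no multiple imputation, so it would need its own imputation model.

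The cost is a few lines of text, a little programming and a less favourable sensitivity result. At 7 v 7 with a true 0.5 SD, the asymmetric run gives 0.5 − 0.10 × 2.91 = 0.21 SD, against 0.45 SD under the present rule.

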***2.2 Secondary endpoints***

The following key secondary endpoints (change per month in physical performance outcome measures) will be investigated:

- chair-stand test
- Timed up and go (TUG) test
- Short Physical Performance Battery (SPPB)

The following secondary endpoints will be also addressed:

- change per month in handgrip strength
- change per month in Tinetti scale
- change per month in Barthel Index
- change per month in activities of daily living (ADL) score
- change per month in body weight
- change per month in appendicular muscle mass (AMM)
- change per month in skeletal muscle mass index (SMMI)
- change per month in cognitive status (Trail making test and Mini Mental State Examination [MMSE])
- change per month in quality of life (Short-Form 12-Item Health Survey [SF-12])
- the proportion of patients who improved their rehabilitation intensity profile
- the modality of discharge (home vs. institution)
- the overall economic benefits (using length of stay [LOS] and total duration of rehabilitation [minutes] as surrogate measures)
- safety of the intervention

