## *6.3 Assessment of safety*

Based on previous trials investigating the use of this food for special medical purposes, the proposed intervention is considered to be safe. Patients will be actively monitored for the occurrence of any potential gastrointestinal side effect associated with the consumption of the nutritional intervention formula (common adverse events). The occurrence of any unexpected serious adverse event will also be recorded.

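### Section 8.2 gives binary endpoints, safety proportions included, a binomial-GLM interval with no provision for small counts; if an event type proves sparse, that interval can be too narrow or not estimable (minor)

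*Protocol*

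**What the plan says.** Protocol section 8.2 sets one method for binary secondary endpoints: "For secondary endpoints on a binomial scale, a generalized linear model for the binomial family will be used". It then fixes what is reported: "For all endpoints the treatment effect (mean or frequency difference) and 95% confidence interval (CI) will be reported". The link function and the type of interval are not named, and small counts get no separate treatment.

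Section 2.2 lists "safety of the intervention" as a secondary endpoint. The other binary endpoints there are "the proportion of patients who improved their rehabilitation intensity profile" and discharge home versus to an institution.

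Section 6.3 says that "the proposed intervention is considered to be safe". It calls for active monitoring of "any potential gastrointestinal side effect associated with the consumption of the nutritional intervention formula (common adverse events"), and adds: "The occurrence of any unexpected serious adverse event will also be recorded". No event rate is given anywhere. Section 8.1 randomizes 70 patients per arm, and section 8.2 puts everyone who took at least one serving in the safety analysis, so the safety denominators are at most 70 per arm.

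**The concern.** A binomial GLM yields a frequency difference directly only with an identity link, and its usual model-based interval is then the Wald interval. In that interval an arm with no events contributes zero variance. With no events in either arm, the report would read as a difference of 0 known exactly. With a few events against none, the interval uses the sampling error of one arm only. With a logit link, an empty arm produces separation and the model has no finite estimate.

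Safety is a named endpoint, and single event types in 70 patients per arm can easily give small counts. At stake is a safety table that shows more certainty than the data hold, or a row that cannot be filled.

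**Working it through.** **Inputs.** n = 70 per arm (section 8.1). Two-sided 95% interval (section 8.2). Identity link with Wald interval: an assumption, being the direct route from the stated model to the stated effect measure. Event rates: assumed over a range, because the protocol gives none. It also states no figure for binary endpoints, so there is none to reproduce.

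**Formulas.** With p1 = x1/70 and p2 = x2/70:
- Wald: (p1 - p2) ± 1.96 × sqrt[p1(1-p1)/70 + p2(1-p2)/70].
- Newcombe: take the Wilson score limits (l, u) of each arm. Lower limit = (p1 - p2) - sqrt[(p1 - l1)² + (u2 - p2)²]. Upper limit = (p1 - p2) + sqrt[(u1 - p1)² + (p2 - l2)²].

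**Example, 4 vs 0.** p1 = 4/70 = 0.0571 and p2 = 0.
- Wald: SE = sqrt(0.0571 × 0.9429/70) = 0.0277, all of it from the arm with events. 0.0571 ± 1.96 × 0.0277 gives 0.3 to 11.2 points.
- Newcombe: Wilson limits are 0.0224 to 0.1379 for 4/70 and 0 to 0.0520 for 0/70. Lower = 0.0571 - sqrt(0.0347² + 0.0520²) = -0.5 points. Upper = 0.0571 + 0.0808 = 13.8 points.

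**Intervals in percentage points, 70 per arm:**

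| Events | Wald | Newcombe |
|---|---|---|
| 0 vs 0 | 0.0 to 0.0 | -5.2 to 5.2 |
| 1 vs 0 | -1.4 to 4.2 | -3.9 to 7.7 |
| 3 vs 0 | -0.5 to 9.0 | -1.6 to 11.9 |
| 4 vs 0 | 0.3 to 11.2 | -0.5 to 13.8 |
| 5 vs 2 | -2.9 to 11.5 | -3.8 to 13.1 |

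**Logit link.** Fitted to 3 vs 0, the standard error of the log odds ratio is about 15,700, which signals separation.

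**Exact coverage of the nominal 95% interval** (all outcomes of two independent binomials enumerated, n = 70 each):

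| True rates | Wald | Newcombe |
|---|---|---|
| 2% / 0.5% | 75.5% | 99.8% |
| 3% / 1% | 87.0% | 99.3% |
| 5% / 1% | 91.5% | 97.8% |
| 1% / 1% | 99.5% | 99.9% |
| 2% / 2% | 97.3% | 99.3% |
| 10% / 5% | 94.0% | 96.0% |
| 20% / 10% | 94.4% | 95.4% |
| 30% / 20% | 94.8% | 95.0% |

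**How often an arm is empty.** If an event type has the same true rate r in both arms, the chance that at least one arm has no events is 1 - [1 - (1-r)^70]². This is 74% at r = 1%, 43% at 2% and 22% at 3%. The chance that both are empty is (1-r)^140: 24%, 6% and 1%.

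**The case against.** **The protocol does not say that events are rare.** A reader might infer from section 6.3 that it expects sparse safety data. It does not: being considered safe is not a rate, and the gastrointestinal effects are described as common. This stands, so sparseness is a condition here and not a stated expectation.

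**Link and interval are not fixed.** A GLM can be paired with another interval, and such detail may sit in a statistical analysis plan that is not shown. This stands in part: the Wald interval is the natural reading, not a stated choice. Still, the rule as written has no exception, and both common links fail with an empty arm, in different ways.

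**Safety may only be described.** Section 8.2 names no binary safety variable and specifies no separate safety comparison. However, it promises a treatment effect with a CI for all endpoints, and section 2.2 lists safety as one of them.

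**False significance.** A reader might infer that the Wald interval will often declare a spurious safety difference. The figures do not support that. At equal rates of 1% and 2% it excludes zero in only 0.5% and 2.7% of trials. The low coverage at unequal rates comes almost wholly from an upper limit that is too low: at 2%/0.5%, 24.3 points of the non-coverage lie there and 0.2 at the lower limit. The 4 vs 0 case is also not clear-cut, because Fisher's exact test gives p = 0.12 but Barnard's exact test gives p = 0.049.

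**A Fisher p-value beside a Newcombe interval can contradict it.** At 5 vs 0 the interval is 0.5 to 15.7 points, excluding zero, while Fisher's p is 0.058. This stands and shapes the fix.

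**Conclusion.** The point holds as a minor, conditional one. Under the identity-link Wald reading with 70 per arm, the interval has zero width at 0 vs 0, where a score interval still allows about 5 points either way. It is too narrow, but not collapsed, when only one arm is empty. Coverage drops to about 75-92% for low, unequal true rates between 2%/0.5% and 5%/1%. It does not drop for equal very rare rates, and it is close to nominal once rates reach about 5-10% or more.

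A reader might extend the point to every binary endpoint. That goes too far: profile improvement and discharge destination are essentially unaffected unless they prove sparse. The event rates are assumptions, since the protocol states none. The primary endpoint and the sample size are not touched.

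**What to change.** Add to section 8.2: *Where either arm has few events (for example fewer than 5), the difference in frequency will be reported with a Newcombe (score) 95% CI in place of the model-based interval from the GLM, and the comparison will be read from that interval.* Do not add a separate Fisher p-value. Keep the binomial GLM for all other binary endpoints.

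The cost is one sentence and no new data or patients. The downside is somewhat wider, conservative intervals for rare events: Newcombe coverage was 97.8% or more in the low, unequal scenarios above.
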